## Observation indexes

6

(1) Clinical efficacy was formulated with reference to practical endocrinology and other relevant references. Apparent effects: Disappearance or significant improvement of clinical symptoms such as pain and numbness in the extremities, restoration, or significant improvement of knee and tendon reflexes, increase of nerve conduction velocity >5 m/s compared with that before treatment. Effects: The reduction of clinical symptoms such as pain and numbness in the extremities, partial restoration of knee and tendon reflexes, and the increase of nerve conduction velocity ≤5 m/s than before. In-effects: No improvement in clinical symptoms such as pain and numbness in the limbs, no improvement in knee and tendon reflexes, and no change in nerve conduction velocity. Total effective rate = (number of effective cases + number of effective cases) ÷ total number of cases × 100%.

(2) Nerve conduction velocity: NDI-092 electromyography was used for neurophysiological testing. Patients were placed in a supine position and the motor conduction velocity (MNCV) of the common peroneal nerve, median nerve, ulnar nerve and tibial nerve, and the sensory conduction velocity (SNCV) of the superficial peroneal nerve and median nerve were measured in a quiet state.

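### The three clinical-efficacy grades are neither exhaustive nor nested, so some patients fit none of them

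*Protocol article*

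**What the plan says.** The protocol article, section 6 (Observation indexes), item (1), defines three grades.

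- Apparent effects: "Apparent effects: Disappearance or significant improvement of clinical symptoms such as pain and numbness in the extremities", then, for reflexes and NCV, "significant improvement of knee and tendon reflexes, increase of nerve conduction velocity >5 m/s compared with that before treatment". The three criteria are listed with commas.
- Effects: a reduction of symptoms, "partial restoration of knee and tendon reflexes, and the increase of nerve conduction velocity ≤5 m/s than before". The criteria are joined by an 'and'.
- In-effects: no improvement in symptoms, "no improvement in knee and tendon reflexes, and no change in nerve conduction velocity". These are also joined by an 'and'.

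The total effective rate has as its denominator "total number of cases × 100". Its numerator prints one term twice; I take it to mean Apparent effects plus Effects.

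Item (2) measures "the motor conduction velocity (MNCV) of the common peroneal nerve, median nerve, ulnar nerve and tibial nerve". It adds sensory velocity in two nerves, the superficial peroneal and the median. That is six measurements on five nerves, since the median nerve is measured for both motor and sensory conduction. Section 7.1 plans follow-up testing to see whether conduction deficits found at the endpoint reverse, so the protocol itself foresees that NCV may fall. Section 8.1 assigns dichotomous data to a chi-squared test and ranked data to a non-parametric test.

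**The concern.** An ordered outcome scale should give every patient exactly one grade, and a better result should never cost a patient a grade. These definitions fail on both counts. The three NCV conditions leave out a fall altogether. The joint conditions leave out patients whose symptoms, reflexes and NCV do not move together. The ceiling on the middle grade means that a larger NCV gain can take a patient out of it without lifting the patient into the top one.

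Assessors would then place such patients by their own judgement, on a scale that is already partly subjective. The three-grade comparison would depend on unwritten choices that may differ between assessors and cannot be reconstructed afterwards.

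**Working it through.** **The plan's own figure.** The design figure in section 5 is the sample size. Inputs: means 6.58 and 5.6 (difference 0.98), SD 1.58, α 0.05 (taken as two-sided, which is the version that matches), power 0.80.

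n per arm = 2 × (1.960 + 0.842)² × 1.58² / 0.98² = 2 × 7.85 × 2.496 / 0.960 = 40.8, so 41 by the normal approximation. The t-test version gives 41.8, so 42 as stated. Adding 10%: 84 × 1.1 = 92.4, so 93. The figure reproduces and rests on the pain score alone. The grades do not enter it.

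**Step 1: try patients against the definitions as written.**

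| Symptoms | Reflexes | NCV change (m/s) | Grade |
|---|---|---|---|
| reduced | partly restored | +3 | Effects |
| reduced | partly restored | +6 | none: above the Effects ceiling, and symptoms and reflexes fall short of Apparent effects |
| pain gone | restored | 0 | none: neither higher grade admits a flat NCV |
| pain gone | unchanged | +3 | none: reflex criterion not met |
| no improvement | no improvement | −2 | none: a fall is not 'no change' |
| no improvement | no improvement | +2 | none: NCV has changed, but nothing else has improved |

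The first two rows show that the scale is not ordered, and the rest that it is not exhaustive.

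**Step 2: count the combinations.** Give symptoms three levels (none, partial, marked), reflexes the same three, and NCV four states (fall, no change, rise ≤5, rise >5): 3 × 3 × 4 = 36 combinations.

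- As written, with all three criteria required: 1 + 1 + 1 = 3 have a grade.
- More generously, let Effects accept partial or better on symptoms and reflexes (2 × 2 × 1 = 4), and let In-effects accept a fall as well as no change (2): 1 + 4 + 2 = 7 have a grade and 29 do not.

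These are counts of combinations, not shares of patients; the combinations are not equally likely.

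**Step 3: illustrate the NCV condition alone.** The documents give no SD of NCV change, so I assume 1 to 4 m/s, a normal distribution and no true change.

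- Read to 0.1 m/s: P(fall) = Φ(−0.05/SD) = 0.480 at SD 1 and 0.495 at SD 4. P(no change) = 1 − 2 × P(fall) = 0.04 and 0.01.
- Read to 1 m/s: P(fall) = Φ(−0.5/SD) = 0.309 and 0.450. P(no change) = 0.38 and 0.10.
- With a true mean rise of 2 m/s, read to 0.1 m/s: P(fall) = Φ(−2.05/SD) = 0.153 at SD 2 and 0.247 at SD 3.

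A fall is therefore a common result under plausible assumptions, even when NCV improves on average.

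**The case against.** **A sensible assessor would read the grades more loosely.** In the lowest grade, 'no change' follows two statements of no improvement and may simply mean no gain. That places patients with no gain on any criterion, including those whose NCV falls. It does not place the patient with relief of pain and flat NCV, or the patient in the second row of the table. The commas in Apparent effects could even be read as alternatives, so that any one top-level result suffices. That grades 36 − 2 × 2 × 3 = 24 combinations; with one for Effects and two for In-effects, 9 of 36 still have no grade, such as reduced pain with unchanged reflexes and a small NCV rise. It would also give the top grade to a patient whose NCV alone improved. No reading closes the gap.

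**The nerve and the tolerance may be set elsewhere.** This is fair. A condensed article may leave both to the full protocol or analysis plan, and I do not count their absence as the fault. The fault is in the grade definitions, which the article does state.

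**Stronger readings.** A reader might infer three things that the documents do not support.

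- That ungraded patients leave the counts. The denominator is all cases, so they can stay in it.
- That measurement noise decides the grade. Where all criteria must hold, noise settles only the NCV condition, and so whether a patient fits a grade. It cannot make a patient effective without symptom and reflex gains.
- That the chance of some measurement rising above 5 m/s by error alone is large. Such a figure needs an error SD, independent errors within a patient and a best-of-six rule. The article gives none of these.

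**Consequences are limited.** This also stands in part. The article does not name this outcome as primary, NCV is compared in its own right in section 7.1, and section 3 blinds patients and physicians, so improvised grading should mainly add noise rather than favour one arm.

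**Conclusion.** The point holds as a fault in a stated definition. Patients with a fall in NCV, with discordant results, or with partial symptom and reflex gains and an NCV rise above 5 m/s fit no grade as written. The three-grade comparison is undefined for them. The total effective rate is defined only if they count as not effective, a rule that the article does not state.

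The share affected cannot be derived from the documents. The statement that about half of patients would show a fall assumes no true change and a finely read scale; coarser reading or a true rise lowers it. The sample size is untouched, so this is a definition worth correcting, not a threat to the trial's design.

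**What to change.** Reword section 6 (1) in three respects.

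1. Define In-effects as every randomised patient who meets neither higher grade, expressly including NCV decline, worsening and discordant results. Read literally, this also takes in patients without an endpoint assessment; if a different rule is wanted for them, state it alongside.
2. Nest the grades. Make the NCV criterion for Effects a rise of at least a stated minimum, with no upper limit, in a patient who does not meet Apparent effects. Treat its symptom and reflex criteria likewise as 'at least' conditions, and say that Apparent effects requires all three criteria.
3. Name in advance the one NCV measurement or summary, out of the six, that sets the grade.

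The cost is the rewording of one outcome definition and its case report form page. The residual rule counts discordant patients as not effective, so the effective rate may be lower than if assessors had graded them leniently. Against the literal text the direction is not fixed: removing the ceiling can only add effective patients, and a stated minimum can only remove some.

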## Sample size

5

By reviewing the relevant literature,^[23]^ the independent statistician obtained the endpoint mean pain score (MPS). The mean value of the effects of the placebo group was 6.58; the standard deviation of the sample of the placebo group was 1.58; the mean value of the effects of the treatment group was 5.6; the standard deviation of the sample of the treatment group was 1.58. It is logged on the sample size calculation website (https://www.biostats.cn/statx/compute.html), and the relevant parameters were set. The 1-β test efficacy was 0.8 at *α* = 0.05 test level, the ratio of the sample size of the test group to the control group was 1:1, and 42 cases were obtained for the placebo group and the treatment group, respectively. Considering a shedding rate of no >10%, it was designed to include cases, and at least 93 patients should be included in this final clinical trial.

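### The printed total effective rate adds the same count to itself and leaves out the best-response grade, so the numerator needs correcting

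*Protocol article*

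**What the plan says.** Section 6 (Observation indexes), item (1), sets out three grades of clinical efficacy:

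- the best grade, with a nerve conduction gain above 5 m/s: "Apparent effects: Disappearance or significant improvement of clinical symptoms such as pain and numbness in the extremities";
- the middle grade, with a gain of at most 5 m/s: "Effects: The reduction of clinical symptoms such as pain and numbness in the extremities, partial restoration of knee and tendon reflexes";
- no response, with conduction unchanged: "In-effects: No improvement in clinical symptoms such as pain and numbness in the limbs".

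It then gives the summary measure: "Total effective rate = (number of effective cases + number of effective cases"), divided by all cases and expressed as a percentage.

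No other section restates or corrects this formula. The abstract names clinical efficacy among the outcomes observed. Section 8.1 assigns a chi-squared test to dichotomous variables and a non-parametric test to rank data.

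**The concern.** A total response rate over three grades should add the two positive grades. The printed numerator repeats one term, and the grade with the largest improvement is not named in it.

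This is the only responder rate that the article defines, and it belongs to an efficacy outcome. If the line were followed as printed, patients with the best response would add nothing to the rate. The result would also not be a proportion of patients, so it could not feed the chi-squared test in Section 8.1. If the analyst instead uses the sensible reading without saying so, the reported rate departs from the published definition against which it will be checked.

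**Working it through.** **Inputs.** Let A, E and I be the numbers graded Apparent effects, Effects and In-effects in an arm, with N = A + E + I (Section 6). Section 5 gives 42 per arm before dropout and 93 in total. The article gives no expected values of A, E or I, so every count below is hypothetical.

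**The plan's own figure.** Section 5 uses means of 6.58 and 5.6 (difference 0.98), SD 1.58, power 0.8 and α = 0.05, taken here as two-sided. With the noncentral t distribution, 41 per arm gives power 0.792 and 42 per arm gives 0.802, so 42 is reproduced. Then 2 × 42 = 84 and 84 × 1.10 = 92.4, which rounds up to 93. (Dividing by 0.90 instead gives 93.3, hence 94; that one-patient difference is not part of this point.) No response rate enters this calculation.

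**The two formulas.**

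- As printed, taking both terms as the middle grade: (E + E)/N = 2E/N.
- As the three grades imply: (A + E)/N.
- Printed minus implied: (E − A)/N. The two agree only when A = E.

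**Above 100%.** 2E/N > 1 whenever E > N/2. With N = 42 and E = 25, 2 × 25/42 = 119%. The matching count of non-responders would be 42 − 50 = −8, so no two-by-two table exists. With N = 46 and grades 10/30/6, the printed rate is 60/46 = 130.4% and the implied rate is 40/46 = 87.0%.

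**Ranking of the arms.** With equal N, the ranking reverses when the arm with the larger A + E has the smaller E.

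| Hypothetical counts (A/E/I) | Implied (A + E)/N | Printed 2E/N |
|---|---|---|
| Mudan 20/10/12, N = 42 | 30/42 = 71.4% | 20/42 = 47.6% |
| Placebo 5/15/22, N = 42 | 20/42 = 47.6% | 30/42 = 71.4% |
| Mudan 25/10/11, N = 46 | 35/46 = 76.1% | 20/46 = 43.5% |
| Placebo 5/20/21, N = 46 | 25/46 = 54.3% | 40/46 = 87.0% |

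Both pairs reverse.

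**A case with no reversal.** With N = 42, an arm with A = 20 and E = 15 has a printed rate of 30/42 = 71.4%, and an arm with A = 5 and E = 10 has 20/42 = 47.6%. The implied rates are 35/42 = 83.3% and 15/42 = 35.7%. The order is kept, although both printed rates are wrong.

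**The case against.** The strongest reply is that this is a self-evident slip. Adding a count to itself serves no purpose. A total made of two terms, directly after two positive grades, points to Apparent-effect plus Effect cases. Nothing in the article suggests that anyone would compute 2E/N. This stands as to intent, and the harm to the result arises only if the line is applied literally. It does not make the printed definition right, and no other section corrects it.

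It can also be said that no grade carries exactly the name used in the numerator, so reading both terms as the middle grade is an inference. That is fair. It does not rescue the formula: if the repeated term meant every patient with any response, the rate would be 2(A + E)/N, which also double counts.

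The outcome's weight should not be overstated. It comes first in Section 6, but the abstract lists visual analog scores ahead of it, Section 6 does not call it primary, and Section 5 sizes the trial on pain score.

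A reader might infer that, under the printed formula, the arm with more Apparent-effect patients always scores lower. The algebra does not support this. The printed rate depends on E alone, and the case with no reversal shows the arm with more such patients scoring higher. Reversal happens only for some distributions.

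A statistical analysis plan that is not shown may state the rate correctly. That would settle the analysis, but the article does not leave the definition to another document. It gives one, and the one it gives is wrong.

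**Conclusion.** The point holds as an error in a printed outcome definition, very probably a wording or translation slip. Read literally, the rate is 2E/N. It differs from the implied rate by (E − A)/N, exceeds 100% when more than half of an arm is graded Effect, and can reverse the arms. These statements follow from the algebra, given that both terms mean the middle grade.

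The size of the error in this trial cannot be stated, because no grade distribution is given. In the 42-per-arm illustration each arm is off by 10/42 in absolute terms: Mudan (10 − 20)/42 = −23.8 percentage points, placebo (15 − 5)/42 = +23.8 percentage points.

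A reader might go on to infer that the trial's reported rate will be wrong, or that the sample size is compromised. The article supports neither: it does not show that the literal formula will be used, and the 42 per arm and the total of 93 do not depend on it. Nor does this error give any reason to change the denominator or the choice of test.

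**What to change.** Correct the numerator and nothing else:

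*Total effective rate = (number of Apparent-effect cases + number of Effect cases) ÷ total number of cases × 100%.*

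Using the grade names from Section 6 also removes the doubt about which patients each term covers. The corrected rate always lies between 0 and 100% and is a proper proportion for the chi-squared test in Section 8.1. The cost is one corrected line, best issued before unblinding. It has no effect on sample size, data collection or visits.

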## Safety

7

### Primary safety parameter

7.1

The primary safety parameter was nerve conduction (NC) and assessed at 3 time points during the study period-baseline, endpoint, and follow-up. The mean NC measurements were compared at baseline and endpoint to determine if there were any changes in NC of nerve fibers during the study period. NC testing was carried out during follow-up to determine if any NC neurological deficits observed at endpoint were reversible 2 weeks after the end of drug treatment. All patients were required to complete the follow-up NC testing, regardless of whether they participated in this study in its entirety.

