### Secondary safety parameter

7.2

Patients’ routine blood, electrocardiogram, and liver and kidney function tests will be checked at baseline, endpoint, and follow-up of the trial, respectively, aiming to assess the safety of the treatment. All information on adverse events will be recorded at all times, including symptoms of adverse reactions, duration, severity of symptoms, management measures, etiology, and patient prognosis and regression. Investigators record, organize, analyze, and summarize in details.

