### Statistical analysis

8.1

The data statistician of Jiangxi health vocational college of Health Professions will apply SPSS 26.0 (IBM Corp., Armonk, NY, USA) software for data processing. Furthermore, the data statisticians will use descriptive statistics to summarize the baseline situation of the 2 groups. According to the type of data information, we will use the mean and standard deviation to describe continuous variables, dichotomous variables will use the chi-squared test, and rank data will be expressed by non-parametric test. *P* < .05 has statistical significance of differences.

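### Primary safety analysis compares nerve conduction from baseline to endpoint only, so it neither attributes a loss to Mudan granules nor bounds how large that loss could be

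*Protocol article*

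**What the plan says.** Primary safety parameter (7.1) names NC as the primary safety measure, taken at baseline, endpoint and follow-up. The stated analysis is: "The mean NC measurements were compared at baseline and endpoint to determine if there were any changes in NC of nerve fibers during the study". The follow-up test, two weeks after treatment ends, asks whether deficits seen at endpoint recover. The section mentions neither the placebo group nor an interval or tolerated loss.

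Statistical analysis (8.1) gives one criterion for the whole article, "P* < .05 has statistical significance of differences". It describes continuous variables by mean and standard deviation and names no test for them.

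Sample size (5) rests on a pain score. "The mean value of the effects of the placebo group was 6.58" and "the mean value of the effects of the treatment group was 5.6", with a standard deviation of 1.58 in both arms. The result is that "42 cases were obtained for the placebo group and the treatment group, respectively".

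Observation indexes (6) lists six conduction velocities: motor for the common peroneal, median, ulnar and tibial nerves, and sensory for the superficial peroneal and median nerves.

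**The concern.** There are two separate weaknesses in the contrast that 7.1 fixes.

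- **Attribution.** A baseline-to-endpoint change contains whatever the drug does plus everything else that happens over 8 weeks: glucose control and other routine care given to both arms (section 4), disease course, and measurement drift. The placebo arm exists to remove that second part, but the stated comparison does not use it. A harm can be masked by a background improvement, and a background decline can be mistaken for a harm.
- **Bounding.** Asking whether any change is detectable does not answer the safety question, which is how much loss the data still allow. Failure to reach P < .05 reflects sample size and measurement noise as well as the drug. The sample size was chosen without reference to NC.

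The article gives the evaluation of safety equal standing with efficacy in its aim. NC is the measure on which it says safety is primarily assessed, so the form of this analysis matters.

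**Working it through.** **Step 1. Reproduce the plan's own sample size.** Inputs from section 5: means 6.58 and 5.6, SD 1.58, alpha 0.05, power 0.8, ratio 1:1. Sidedness is not stated; two-sided is used because it reproduces the stated n.

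- Difference = 6.58 − 5.6 = 0.98; standardised, 0.98/1.58 = 0.62 SD.
- Two-sided two-sample t-test (non-central t): power at 42 per arm is 80.2%. The normal approximation gives 41 per arm.
- Dropout: 84 × 1.10 = 92.4, rounded up to 93.

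The figures of 42 per arm and 93 in total are reproduced. Every input is a pain-score input; none concerns NC.

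**Step 2. Precision of an arm difference in NC.** The article gives no NC standard deviation, so results are in SD units.

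- Half-width of the 95% CI, unadjusted, 42 per arm: t(0.975, 82) × √(2/42) = 1.989 × 0.218 = 0.43 SD.

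An estimated difference of exactly zero would therefore still be compatible with a loss of about 0.43 SD.

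**Step 3. Miss rate of a between-arm t-test.** Two-sided 5%, 42 per arm, non-centrality d × √(42/2). The true losses d are assumed:

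- d = 0.3: missed in 72.6%
- d = 0.4: missed in 55.9%
- d = 0.5: missed in 38.0% (34.0% at 46 per arm)
- d = 0.8: missed in 4.8%

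**Step 4. Miss rate of the contrast that 7.1 describes.** Paired test in one arm of 42, loss of 0.5 SD of the measurement, baseline-endpoint correlation ρ assumed. Standardised change = 0.5/√(2(1 − ρ)); non-centrality = that value × √42.

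- ρ = 0.3: 0.5/1.183 = 0.423; missed in 23.8%
- ρ = 0.5: 0.5/1.000 = 0.500; missed in 11.4%
- ρ = 0.7: 0.5/0.775 = 0.645; missed in 1.7%

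These rates are lower, but they concern the total change within one arm. They equal miss rates for a drug effect only if nothing else moves NC over 8 weeks.

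**Step 5. What baseline adjustment gains.** Adjusting endpoint NC for baseline multiplies the residual SD by √(1 − ρ²). The half-width from step 2 becomes approximately:

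- ρ = 0.3: 0.434 × 0.954 = 0.41 SD
- ρ = 0.5: 0.434 × 0.866 = 0.38 SD
- ρ = 0.7: 0.434 × 0.714 = 0.31 SD

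The corresponding between-arm miss rates for a 0.5 SD loss are 34.0%, 25.6% and 11.3%.

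**Step 6. What a formal margin would cost.** Assume a margin of 0.5 SD, one-sided 0.025 and no true difference. For 80% power, n = 2 × (1.96 + 0.842)²/0.5² = 62.8, so 63 per arm. At 42 per arm a harmless drug would fail that margin about 38% of the time. The smallest margin supported with 80% power is (1.96 + 0.842) × √(2/42) = 0.61 SD.

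**The case against.** The strongest reply is that the article never says a non-significant NC result means no change, or that the drug is safe. That is correct. A reader might infer such a rule from the wording of 7.1 together with the P < .05 line, but no sentence states it, and the P < .05 line is a general convention not tied to NC.

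A reader might also take 38% as the chance that this trial misses a nerve harm. The documents do not support that. The figure belongs to an unadjusted between-arm test with an assumed loss of 0.5 SD, whereas 7.1 describes baseline versus endpoint. Six velocities are measured, so a single-test rate is not the miss rate of the trial either.

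Nor can the point be extended to adverse events. Secondary safety parameter (7.2) says the laboratory and ECG checks are made "aiming to assess the safety of the treatment" and that events are recorded and summarised; it names no test. It would also be wrong to say that 7.1 ignores direction, since the follow-up test for reversible deficits shows that loss is what it looks for.

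Finally, margins and intervals are often left to an analysis plan, which is not shown here. This disposes of any complaint that a margin is absent. It does not dispose of the point itself, because 7.1 does specify a contrast, and that contrast leaves out the placebo arm.

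**Conclusion.** The point holds in a limited form. As written, the primary safety analysis would neither attribute a change in NC to the drug nor bound a loss. This rests on the wording of 7.1, the single criterion in 8.1 and the pain-only sample size in section 5. It does not depend on any one miss rate.

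The size is illustrative only, because NC variability, correlation and a relevant loss are all assumed. An unadjusted arm difference would carry a half-width of about 0.43 SD. Miss rates run from about 73% to 5% between arms for losses of 0.3 to 0.8 SD. For a 0.5 SD loss in a paired test they run from about 24% to 2% at correlations of 0.3 to 0.7.

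The documents do not show that the trial will declare the drug safe on P > .05. They also do not make a non-inferiority margin necessary. This is a free improvement to the stated analysis.

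**What to change.** In 7.1, replace the baseline-versus-endpoint comparison with the Mudan-minus-placebo difference in endpoint NC, adjusted for baseline NC, for each of the six velocities in section 6, with its 95% CI. Base the safety statement on the largest loss each interval allows, in m/s, and say that P > .05 is not in itself evidence of safety. The follow-up measurement can stay as it is for reversibility.

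A formal loss margin is optional. If the investigators want one, they should fix it before unblinding, say which nerves it covers, and accept the failure rate shown in step 6 at the present size. The 5 m/s in section 6 is a per-patient cut-off for improvement and should not be carried over as a margin for mean loss.

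The cost is a few sentences in 7.1 and 8.1. No patients, visits or measurements are added, since baseline and endpoint NC are already collected.

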### Study design

2.1

This is a randomized, double-blind, and placebo-controlled design. A total of 93 patients with painful diabetic neuropathy recruited in this study will be randomized at the ratio of 1:1 to receive treatment and placebo groups for 8 weeks, and the evaluators will assess and analyze the outcomes at 3 time points (pre-treatment, 8 and 10 weeks). The Jiangxi health vocational college will be responsible for data management and statistics. The flow chart of the trial is shown in Fig. 1.

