#### Inclusion criteria

2.3.2

(1)Patients diagnosed with type 2 diabetes according to the criteria of WHO in 1999, aged from 40 to 70;(2)Patients presented with obvious spontaneous neuralgia and numbness and other neuropathic symptoms, which were obvious in both lower limbs, and the pain was like burning knife to cut worms and dragging and needling, often accompanied by aggravation at night and/or sleep disturbance. Most importantly, the symptoms lasted for >6 months;(3)Electromyography showed a decrease in motor sensory nerve conduction velocity (MNCV <45 m s^−1^, SNCY <45m s^−1^);(4)Patients with pain visual analogue score (VAS) >4, without analgesic medication in the last 1 week;(5)Michigan neuropathy screening instrument (MNSI) >2 point.(6)Fasting blood glucose <8 mmol/L; 2 hours postprandial blood glucose <15 mmol/L, glycosylated hemoglobin <8.5%.

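### The primary safety contrast for nerve conduction is stated only as baseline versus endpoint, so a drug effect cannot be separated from regression to the mean and shared time trends

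*Protocol article*

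**What the plan says.** - **Role and timing (Section 7.1).** "The primary safety parameter was nerve conduction (NC) and assessed at 3 time points during the study period-baseline, endpoint, and follow-up".
- **Comparison (Section 7.1).** "The mean NC measurements were compared at baseline and endpoint to determine if there were any changes in NC of nerve fibers". No arm is named.
- **Follow-up (Section 7.1).** Testing is repeated "to determine if any NC neurological deficits observed at endpoint were reversible 2 weeks after the end of drug treatment". Again no arm is named. The section also requires follow-up NC testing of every patient, including those who did not complete the study.
- **Entry (Section 2.3.2, criterion 3).** "Electromyography showed a decrease in motor sensory nerve conduction velocity", with cut-offs of 45 m/s for motor and sensory velocity.
- **Design (Section 2.1).** Patients are "randomized at the ratio of 1:1 to receive treatment and placebo groups for 8 weeks", so a concurrent control exists.
- **Common care (Section 4).** Both arms receive routine diabetes care, including glucose, blood pressure and lipid control.
- **Statistical methods (Section 8.1).** Continuous variables are to be summarised by mean and SD. A chi-squared test is named for dichotomous data and a non-parametric test for ranked data. No between-arm test is named for continuous data.

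**The concern.** A safety question in a randomised placebo-controlled trial is whether the drug changes nerve conduction relative to placebo. The contrast in Section 7.1 asks instead whether mean conduction changed over time. That change has at least three components: the drug effect, regression to the mean after selecting low values, and anything that shifts both arms over 8 weeks, such as routine care. A before-after comparison cannot separate them. Randomisation removes the last two, in expectation, from the difference between arms.

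The direction matters. Patients selected for low velocity are expected to measure somewhat higher on retest, so regression to the mean works against finding a fall. Real slowing could then be reported as no change. The reversibility question has a related weakness: a deficit identified at endpoint is partly measurement error and tends to shrink on retest. Apparent recovery two weeks later therefore does not by itself show that a drug effect has reversed.

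**Working it through.** **Inputs from the documents.** Entry cut-off 45 m/s (Section 2.3.2); 1:1 randomisation (Section 2.1); 42 per arm (Section 5). The documents give no mean, SD or retest reliability for conduction velocity, so those below are assumptions.

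**The plan's own figure.** Section 5 sizes the trial on pain score: difference 6.58 − 5.6 = 0.98, SD 1.58, power 0.80, alpha 0.05. With a two-sided test, 2 × (1.58 × (1.960 + 0.842) / 0.98)² = 40.8, and the t-test version gives 41.8, so 42 per arm is reproduced. Nothing was sized for NC; 42 is used below only as the available number.

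**Expected drift with no drug effect.** Let velocity before selection be normal with mean μ and SD s, with retest correlation r, and let patients enter only if the value is below 45. If that value is also the baseline,

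drift = (1 − r) × s × φ(a)/Φ(a), with a = (45 − μ)/s.

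| μ | s | r | φ(a)/Φ(a) | Drift (m/s) |
|---|---|---|---|---|
| 38 | 4 | 0.95 | 0.090 | +0.02 |
| 38 | 5 | 0.90 | 0.163 | +0.08 |
| 40 | 5 | 0.90 | 0.288 | +0.14 |
| 45 | 6 | 0.95 | 0.798 | +0.24 |
| 45 | 5 | 0.80 | 0.798 | +0.80 |
| 45 | 6 | 0.80 | 0.798 | +0.96 |
| 48 | 6 | 0.70 | 1.141 | +2.05 |

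The first and last rows are the extremes over means 38 to 48, SD 4 to 6 and reliability 0.70 to 0.95. The sign is always positive; the size varies about a hundredfold.

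**What this does to a true slowing of 1 m/s.** Take μ = 45, s = 6, r = 0.80.

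- Variance of baseline after selection: 36 × (1 − 2/π) = 13.08.
- SD of change: √[(1 − 0.8)² × 13.08 + 36 × (1 − 0.64)] = √13.48 = 3.67.
- Before-after in the Mudan arm: expected change 0.96 − 1 = −0.04; SE 3.67/√42 = 0.57. Probability of a significant decline: Φ(−1.96 + 0.04/0.57), about 3%. Without the drift it would be Φ(−1.96 + 1/0.57), about 42%.
- Between arms, on change: expected difference −1, because the drift cancels; SE 3.67 × √(2/42) = 0.80. Power: Φ(1/0.80 − 1.96), about 24%.
- Between arms, adjusted for baseline: SE 6 × √(1 − 0.64) × √(2/42) = 0.79, so the 95% CI is about ±1.5 m/s.

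With r = 0.95 and the same μ and s, the drift is 0.24 m/s. The before-after test then finds the decline about 75% of the time and the between-arm test on change about 68%. Over the whole grid, between-arm power for 1 m/s runs from about 17% to 95%. The gain from the between-arm contrast is freedom from this bias; it does not guarantee more power.

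**The case against.** The strongest reply is that this is one condensed sentence in a journal article. It does not say that the arms are pooled, and it does not forbid comparing change by arm. The trial is parallel-controlled, NC is measured in both arms, and tests for safety variables are often left to an analysis plan that is not shown. This stands in part: a reader might infer that the sponsor has decided to discard the placebo arm, and the documents do not say so. But the article does not leave the contrast open. It states one, and Section 8.1 supplies no other.

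Several further objections stand:

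- **Size of the drift.** It rests wholly on assumed inputs. Entry also requires symptoms for more than 6 months and MNSI above 2, so the pre-selection mean may lie well below 45, where the drift is small.
- **Selection mechanism.** The entry criterion does not say which nerve, or how many, must be below 45 m/s, while Section 6 measures several. Nerves that did not determine entry need not show the full drift. Nor is it stated that the qualifying test is the baseline; a separate baseline test would shrink the drift.
- **Reversibility.** All patients have follow-up testing, so the data are not confined to those with a deficit, and the deficits in question may be meant at group level. The missing piece is the comparison with placebo.
- **Two roles for one measurement.** Section 6 also uses velocity for efficacy ("increase of nerve conduction velocity >5 m/s compared with that before treatment"). A reader might infer that NC must be reclassified and adverse events made primary. That is a preference: velocity can move either way, and adverse events and laboratory tests are already collected.

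**Conclusion.** The point holds as a fault in the stated contrast and should be fixed. Followed as written, Section 7.1 answers the primary safety question without the randomised comparison, and its answer mixes any drug effect with regression to the mean and common time trends. Neither the follow-up check nor Section 8.1 repairs this.

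The direction of regression to the mean is upward, towards masking harm, provided the qualifying electromyogram serves as baseline and retest reliability is below 1. Its size is unknown: 0.02 to 2.05 m/s over the assumed grid. The direction of any shared time trend is also unknown.

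A reader might infer that slowing of this size would show up clearly between arms. The numbers do not support that: power is about 24% for 1 m/s in the worked case and about 23% for 0.8 m/s with SD 5 and reliability 0.80 (baseline-adjusted SE 5 × 0.6 × √(2/42) = 0.65). The between-arm estimate is free of this bias but may be imprecise, so a non-significant P must not be read as absence of harm.

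**What to change.** In Section 7.1, replace the baseline-versus-endpoint comparison with the Mudan-minus-placebo difference in NC at week 8, adjusted for baseline NC (analysis of covariance), reported with a 95% CI. For reversibility, specify the same adjusted difference at week 10 in all randomised patients, not only in those with a deficit at endpoint. State that harm will be judged from the confidence limit on the side of slowing, not from whether P falls below .05. Add a sentence saying whether the qualifying electromyogram is also the analysed baseline. Before-after summaries within each arm can stay as description.

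The cost is wording only. NC is already planned at baseline, endpoint and follow-up, so no visit, test or patient is added. The change should be made before the data are unblinded.
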